#### Intervention description {11a}

Participants will be randomized to either a 3-week estradiol (100 μg/day, via Climara® patch, or its generic) or placebo treatment. Four weekly clinical assessments will be conducted (baseline, week one, week two, and at the end of treatment) to assess changes in anhedonia and psychosis symptoms as well as blood serum levels of estradiol. Furthermore, participants will complete PET-MR scans at baseline and the end of treatment to examine neural and molecular responses to rewards.

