## Assignment of interventions: allocation

### Sequence generation {16a}

Computer-generated randomization allocated participants to either active or placebo treatment condition without stratification.

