## Statistical methods

### Statistical methods for primary and secondary outcomes {20a}

The first objective of this study is to examine baseline (i.e., pre-treatment) associations between anhedonia and psychosis and neural and molecular responses to rewards. Associations between clinical measures and mechanistic outcomes will be estimated via correlation analysis. The second objective is to evaluate the experimental effects of estradiol versus placebo on clinical outcome measures and mechanistic outcomes. Mixed effects models will be used to examine the effects of time, treatment group, and their interaction on clinical outcomes (four timepoints, random intercept and slope) and neural and molecular outcomes (two timepoints, random intercept only), with age as a covariate. A separate model will be generated for each clinical outcome measure (anhedonia and psychosis) and each neural and molecular outcome (activation during reward anticipation and BP_ND_ and task-related ΔBP_ND_ for striatal regions of interest). Exploratory whole-brain analyses will also be conducted for fMRI activation during reward anticipation. Within the estradiol treatment group only, we will examine how biomarkers of reward response predict changes in clinical outcome measures. We will examine intercorrelations between anhedonia or psychosis and neural and molecular reward response, using residualized gain scores to quantify changes in clinical measures. We will also use mixed effect models to examine how changes in neural and molecular reward response predict variability in clinical outcome trajectories, with a separate model for each clinical outcome and each neural and molecular change score. Maximum likelihood estimation will be used in all mixed effect models to accommodate missing data (e.g., SAS proc mixed). When multiple comparisons are conducted to test a hypothesis, appropriate correction will be applied to achieve a corrected *p*-value of 0.05. For clinical outcome hypotheses, both a per-protocol and an intent-to-treat analytic approach (e.g., utilizing all available data, even for participants who did not finish treatment to completion) will be used. For mechanistic hypotheses, a per-protocol approach will be used, including only participants who completed the baseline PET-MR scan, 3 weeks of estradiol treatment, and the post-treatment PET-MR scan.

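### The estradiol-versus-placebo models are valid, but for the two-scan outcomes they reduce to a change-score comparison that age cannot sharpen; conditioning on the baseline value would be more precise

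*Protocol article*

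**What the plan says.** Section {20a} of the protocol article sets out the treatment comparison: "Mixed effects models will be used to examine the effects of time, treatment group, and their interaction on clinical outcomes". The clinical outcomes have "four timepoints, random intercept and slope". The imaging outcomes are described as "neural and molecular outcomes (two timepoints, random intercept only), with age as a covariate". No other covariate and no equal-baseline constraint is stated for this comparison.

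Baseline is one of the modelled occasions in both cases. Intervention description {11a} says "Four weekly clinical assessments will be conducted (baseline, week one, week two, and at the end of treatment" for symptoms, and "participants will complete PET-MR scans at baseline and the end of treatment" for imaging. Sequence generation {16a} says "Computer-generated randomization allocated participants to either active or placebo treatment condition without stratification".

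The mechanistic analysis set is restricted to completers, "including only participants who completed the baseline PET-MR scan, 3 weeks of estradiol treatment, and the post-treatment PET-MR scan", and on estimation the section says "Maximum likelihood estimation will be used in all mixed effect models to accommodate missing data".

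Adjustment for baseline appears in only one place in {20a}: the correlations within the estradiol arm, where clinical change is expressed as a residualised score.

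**The concern.** A group main effect lets each arm have its own baseline mean, although randomisation makes the two expected means equal. The interaction therefore subtracts the whole observed baseline difference instead of the fraction that predicts follow-up. When baseline and follow-up correlate imperfectly, this adds noise.

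The single named covariate does not help. Age is effectively constant over three weeks, so as a main effect it shifts both occasions equally and leaves the change contrast untouched.

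At stake is precision on the primary mechanistic endpoint, where the protocol expects about 85 analysable women and each extra woman would need two PET-MR scans. Recruitment is also spread deliberately over four severity strata while allocation is unstratified, so nothing in the design balances baseline severity between arms.

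**Working it through.** **Inputs.** From the protocol: 85 analysable women, 43 in the estradiol arm (Sample size {14}), hence 42 on placebo; two scans or four visits; fixed and random effects as quoted. Assumed: rho, the SD ratio between occasions, and the covariance of the clinical scores, none of which is given. I read the completer set as including placebo completers.

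**The protocol's own figures.** Sample size {14} gives smallest detectable f² of .07 (brain) and .05 (clinical) at 80% power with 85 participants. Take a 1-df F test with noncentrality f² × N. With N=85, f²=.07 gives 67% power two-sided and 78% one-sided; f²=.05 gives 53% and 66%. Counting 170 observations, f²=.05 gives 82.6% two-sided. No single reading returns both figures, and the within-person correlation they would need is not stated. The results below are therefore relative to the planned model and not tied to those figures.

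**Two scans, planned model.** With complete data and unit SDs, the interaction is the difference in mean change, with variance 2(1−rho)(1/43+1/42). At rho=.5 this is 1 × 0.04707 = 0.0471. A generalised least squares calculation gives 0.047065 both with and without age as a main effect.

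**Two scans, conditioning on baseline.** The variance is (1−rho²)(1/43+1/42). At rho=.5 this is .75 × 0.04707 = 0.0353. The ratio is (1−rho²)/[2(1−rho)] = (1+rho)/2. If the planned model had 80% power two-sided, the adjusted one would have Φ[(1.960+0.842)/√ratio − 1.960]. The equivalent sample is 85/ratio, and the detectable effect falls by 1−√ratio.

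| rho (assumed) | variance ratio | equivalent N | power if planned = 80% | detectable effect smaller by |
|---|---|---|---|---|
| .3 | .65 | 131 | 93.5% | 19% |
| .5 | .75 | 113 | 89.9% | 13% |
| .7 | .85 | 100 | 86.0% | 8% |
| .8 | .90 | 94 | 84.0% | 5% |
| .9 | .95 | 89 | 82.0% | 2.5% |

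**Unequal SDs.** With k = baseline SD / follow-up SD, the ratio is (1−rho²)/(k²+1−2·rho·k). At k=.8 it is .75/.84 = .89 for rho=.5 and .51/.52 = .98 for rho=.7. At k=1.2 the gain is larger: .75/1.24 = .60 for rho=.5.

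**Chance imbalance.** The baseline difference between arms has a standard error of √(1/43+1/42) = 0.217 SD. Given the observed imbalance, a change score is off by (1−rho) times it: for a one-SE imbalance at rho=.5, .5 × 0.217 = 0.11 SD.

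**Four visits, random intercept and slope.** I took visits at weeks 0 to 3 and total baseline variance 1, with intercept variance .5, .7 or .8; slope variance .005, .02 or .05; and intercept–slope correlation −.3, 0 or .3. Common-baseline against free-baseline variance of the linear slope contrast ran from .68 to 1.00. It reached 1.00 when intercept variance and slope variance were large and their correlation positive. Age again changed nothing with complete visits.

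**A trap in the remedy.** I simulated two-occasion data (n=85, rho=.5, no true effect) and fitted the common-baseline mixed model with the outcome's own baseline, by time, added as a covariate. The model SE was about .13 against an empirical SD of .18 to .19, and type I error was about 16 to 17%. ANCOVA, the plain common-baseline model and the planned model all stayed near 5%.

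**The case against.** The strongest reply is that nothing here is wrong. Group, time and their interaction in a mixed model is a standard analysis of a randomised trial, the protocol claims no baseline-adjusted precision, and a more efficient alternative exists for many sound plans. That stands: the point concerns efficiency.

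A reader might infer that the baseline measurements are discarded. They are not. Baseline is a modelled occasion for every outcome and enters the contrast as a change score; only the extra gain from conditioning on it is forgone. A reader might also infer that the treatment estimate is biased because allocation was unstratified. Averaged over randomisations it is not; the 0.11 SD above is conditional on a particular imbalance.

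It can also be said that a statistical analysis plan, not shown here, may settle the parameterisation. It may, but the article already names the fixed effects, the random effects and the covariate, so a stated choice is under review and not an omission.

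Finally, equal expected baseline means hold for all randomised women, not necessarily for completers. This is a fair limit on imposing a common baseline in the mechanistic set. It does not count against ANCOVA, which needs no such constraint.

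**Conclusion.** The point holds as an inexpensive gain in precision. For BOLD activation, BP_ND and ΔBP_ND, conditioning on baseline cuts the variance of the treatment contrast by 35% at rho=.3, 25% at .5, 15% at .7, 10% at .8 and 5% at .9, given equal SDs at the two scans. These are conditional on an unknown rho and SD ratio, so no single loss of power can be attributed to the plan. For SHAPS and BPRS the saving is about 0 to 32% over the covariances tried, and may vanish.

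The statement about age is exact for complete data, which fits the two-scan completer set; missing clinical visits could give age a slight effect. It would go too far to conclude that every baseline severity measure should be added with a time interaction to the existing mixed model: for SHAPS and BPRS, the outcome's own baseline would then sit on both sides of the equation and the test would be anti-conservative.

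**What to change.** - **BOLD, BP_ND and ΔBP_ND:** ANCOVA of the follow-up value on treatment, the baseline value of the same outcome, and age.
- **SHAPS and BPRS:** one of two forms, named in advance. Either keep the maximum likelihood mixed model with all four visits and give the arms a common baseline mean (drop the treatment main effect; keep time and treatment by post-baseline time); or model the three post-baseline visits only, with the baseline score as covariate.
- **In either case:** do not enter an outcome's own baseline as a covariate while it is also a response.
- **Age:** if it is meant to sharpen the contrast, give it an age-by-time term in the longitudinal models or use the ANCOVA form.

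The cost is a small change to model wording and code, and one degree of freedom per covariate. No extra data are needed. The gain will be small if rho proves high. No interim outcome analysis is planned, so the change can be fixed before any unblinded outcome analysis.

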### Eligibility criteria {10}

The study will include unmedicated, perimenopausal outpatient women ages 44–55 who are in late perimenopause and experiencing anhedonia and/or psychosis symptoms with onset coinciding with perimenopausal menstrual irregularity. To determine participant eligibility, women will undergo initial online and phone screening, the structured clinical interview for the DSM-5 (SCID-5), laboratory testing, and a pelvic exam/PAP test (or a medical records review for an exam within 3 years). Participants must meet the following inclusion criteria to be enrolled in the study:44–55 years old, unmedicated, naturally perimenopausal woman in stage −1 of the Stages of Reproductive Aging Workshop (STRAW) criteria [36, 37]At least mild perimenopausal-onset anhedonia (SHAPS≥20) (Snaith et al. [38])Absent-to-moderate perimenopausal-onset psychosis spectrum symptoms as measured by the Brief Psychiatric Rating Scale (BPRS-Positive Symptom Subscale Score between 6 and 17) (Hafkenscheid [39]; Overall & Gorham [40])

Dimensional measures of anhedonia and psychosis severity are used to stratify participants. With respect to stratification, equal numbers of participants will be recruited into each of the following four strata:Mild-to-moderate anhedonia + absent-to-mild psychosisMild-to-moderate anhedonia + moderate psychosisHigh anhedonia + absent-to-mild psychosisHigh anhedonia + moderate psychosis

Mild–moderate anhedonia severity is defined in this trial as Snaith–Hamilton Pleasure Scale (SHAPS [38]) scores between 20 and 36, and high anhedonia severity is defined as SHAPS>36 (using the ordinal scoring of Franken et al. [41]). There is no widely accepted clinical cut-off on the SHAPS, though a meta-analysis by Trøstheim and colleagues (2020) [42] reported that caseness is indicated by scoring more than 1.96 SDs above the general population, which would correspond to a SHAPS score of 25 or greater (see also Alsayednasser and colleagues [43]). However, in this trial, a SHAPS score cutoff of >20 was used to indicate at least mild, clinically impairing anhedonia, consistent with the cutoff used in the NIMH Fast-Fail Trial for Mood and Anxiety Disorders [38, 44]. The SHAPS has shown adequate psychometric properties in clinical and non-clinical samples [45], and ROC analyses suggest that a SHAPS score of ≥ 20 corresponds to clinically significant anhedonia from a general population sample [38].

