Absent-to-mild psychosis severity is defined in this trial as <6 on the Brief Psychiatric Rating Scale (BPRS) positive symptom subscale [39, 40], consisting of four items: conceptual disorganization, suspiciousness, hallucinations, and unusual thought content. This total indicates a score of “very mild” on any two symptoms or at least mild on any one symptom (control samples typically score absent or “very mild” on these items [46]). “Moderate” psychosis will correspond to BPRS positive symptom subscale scores between 6 and 16, representing one standard deviation above the mean score for patients with psychotic major depression [47]. Additionally, at least one subscale item score must be > 4 to ensure that the psychosis symptom is associated functional impairment. Individuals with psychotic major depression typically have BPRS positive symptom subscale scores between 7 and 11, and a score of 6 best differentiates psychotic MDD from nonpsychotic MDD [47].

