### Methods for additional analyses (e.g., subgroup analyses) {20b}

No subgroup analyses on the outcomes are planned, though suspension or premature discontinuation and closure of the study may occur if the participation in study procedures poses unexpected, significant, or unacceptable risk, as described in section {22} addressing adverse events.

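### The BPRS psychosis model omits the psychosis stratum, although half the women start within one point of the scale floor, so the treatment effect is a diluted average tested with avoidable slope noise

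*Protocol article*

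**What the plan says.** - **Strata.** The article's Eligibility criteria {10} say that "equal numbers of participants will be recruited into each of the following four strata"; two of the four are absent-to-mild psychosis and two are moderate.
- **Low strata.** "Absent-to-mild psychosis severity is defined in this trial as <6 on the Brief Psychiatric Rating Scale (BPRS) positive symptom subscale", a subscale "consisting of four items: conceptual disorganization, suspiciousness, hallucinations, and unusual thought content". The cut-off total is explained as very mild "on any two symptoms or at least mild on any one symptom".
- **Moderate strata.** Moderate "psychosis will correspond to BPRS positive symptom subscale scores between 6 and 16", and in addition "at least one subscale item score must be > 4".
- **Model.** Statistical methods {20a}: "A separate model will be generated for each clinical outcome measure (anhedonia and psychosis"). For clinical outcomes the terms are time, treatment group and their interaction over four timepoints, with random intercept and slope and age as covariate. Neither the psychosis stratum nor a stratum interaction appears.
- **Subgroups.** Section {20b}: "No subgroup analyses on the outcomes are planned".
- **Allocation.** Section {16a}: randomization is not stratified.
- **Power.** Sample size {14} gives one detectable effect, f² = .05 at 80% power with 85 women, for both clinical outcomes.

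**The concern.** Objective 2 expects estradiol to relieve psychosis symptoms more than placebo. By design about half of the women have almost no room to fall on the scale that measures this. SHAPS has no such problem: entry is at 20 or above on a scale that starts at 14.

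Two consequences follow for the BPRS model. First, the group-by-time effect averages women who can move a long way with women who can fall by 0 or 1 point, so its size describes the recruited mix and not women with psychosis symptoms. Second, moderate women can improve on placebo or by regression to the mean, and low-stratum women hardly can. A model that ignores a stratum already recorded at entry puts that predictable difference into the slope variance and loses precision. A small or null BPRS result would then be hard to read as an absence of effect on psychosis.

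**Working it through.** **1. Floor and room to fall.** A total of 6 equals two items at very mild, or one item at mild, only if absent = 1, very mild = 2 and mild = 3: 2+2+1+1 = 3+1+1+1 = 6. The four-item minimum is therefore 4. The article does not state this; it is derived from its explanation.
- Low strata (below 6): scores 4 or 5, room to fall 0 or 1 point.
- Moderate strata (one item above 4): lowest total 5+1+1+1 = 8, highest 16, room to fall 4 to 12 points.

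**2. The plan's power figure.** With a 1-df F test and noncentrality f² × N, f² = .05 gives 53% power at N = 85 and 98% at 340 independent observations. For 80%, about 157 effective observations are needed. With design effect 1 + 3ρ, 340/(1+3ρ) = 157 gives ρ ≈ 0.39. The article states no correlation, so the figure can be neither confirmed nor refuted. It makes no allowance for the floor.

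**3. Dilution.** Let δ be the effect in the moderate strata and e·δ the effect in the low strata. With equal shares, the all-women effect is 0.5(1+e)δ.
- e = 0: 0.50δ.
- e = 1/3 (for example 1 point against 3): 0.67δ.

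**4. Precision.** All inputs here are assumptions, because the article gives no BPRS effect, SD or correlation. Change SD is 1 in the moderate strata and 0.2 in the low strata; the effect is 0.9 in the moderate strata and 0 in the low; placebo improvement is p in the moderate strata and 0 in the low; 85 women, about 42.5 per arm, unstratified, two-sided 5%.

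Without the stratum term, the variance of change is an average within-stratum part, (1 + 0.04)/2 = 0.52, plus a between-strata part:
- placebo arm: 0.52 + 0.25p²
- estradiol arm: 0.52 + 0.25(p + 0.9)²

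The expected estimate is 0.45 and SE = √[(sum of the two)/42.5].

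| p | SE | Power, formula | Power, simulation |
|---|---|---|---|
| 0 | √(1.2425/42.5) = 0.171 | 75% | 77% |
| 0.5 | √(1.5925/42.5) = 0.194 | 64% | 66% |
| 1 | √(2.1925/42.5) = 0.227 | 51% | 50% |
| 1.5 | √(3.0425/42.5) = 0.268 | 39% | 37% |

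With stratum as a covariate and all women kept, p drops out. The residual variance is 0.52 + 0.225² = 0.571 (the second part is the differing effect around its mean), SE = √(4 × 0.571/85) = 0.164, and power is Φ(0.45/0.164 − 1.96) ≈ 78%. Simulation gives 79% to 82% at every p.

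**5. Restricting to moderate women instead.** Under step 4 this also gives about 82%, so it gains almost nothing over adjustment. If δ would give 80% power when all 85 women respond, about 43 women give Φ(2.80 × √0.5 − 1.96) ≈ 51%. If the low strata have 20% of the moderate effect, the adjusted all-women test has 92% to 93% power against 82% to 83% for moderate women alone.

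**The case against.** The best counter-argument has four parts.

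- **Sampling is deliberate.** Severity is treated dimensionally, the spread serves the baseline correlations of objective 1, and the average over enrolled women is a conventional randomized comparison. This stands: the all-women estimate is not biased for that average.
- **Baseline adjustment is often left to an analysis plan, which is not shown.** This stands in part. A stratum covariate is not a subgroup analysis, so section {20b} does not forbid it. But the article lists the model terms and names age as the covariate, and as written that model omits the stratum.
- **The primary endpoints are mechanistic.** True, and it limits the impact, although section {18a} calls SHAPS and BPRS the primary clinical outcomes.
- **The strata are themselves in doubt.** The inclusion criterion asks for a BPRS subscale score of 6 to 17, which read literally empties the strata below 6. That conflict is separate and must be reconciled; the present point takes the four strata as intended.

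A reader might also infer that low-stratum women cannot improve, that the effect is therefore halved, and that the analysis should be confined to moderate women. The documents do not support this. A score of 5 can fall to 4, and scores can rise, so estradiol could still separate from placebo by preventing worsening. Halving needs a zero effect in the low strata. The power loss comes from the missing stratum term, not from keeping these women.

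**Conclusion.** The point holds in a limited form. If the strata are recruited as described, half the sample is at or within one point of the implied BPRS floor, and the stated psychosis model takes no account of it. The all-women effect is a valid average, diluted to about 50% to 67% of the moderate-strata effect when the low strata respond between zero and one third as much.

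The loss of power depends on assumptions. It is slight with no placebo change (about 77% against 80%) and large only with a strong placebo response (about 37% against 80% at 1.5 SD). The documents fix none of these inputs, so no single power figure can be asserted. The interpretive gap does not depend on them: as planned, a null BPRS result would not show whether women with moderate psychosis symptoms benefit. The primary mechanistic endpoints are unaffected.

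**What to change.** First reconcile the inclusion range with the stratum definitions, so that every enrolled woman belongs to one psychosis stratum. Then:

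1. Add baseline psychosis stratum (as defined for recruitment in Eligibility criteria {10}) and stratum by time to the BPRS mixed model, with residual variance allowed to differ by stratum.
2. Keep the all-women adjusted treatment effect.
3. Prespecify stratum by group by time, and report the effect in the moderate-psychosis strata beside the all-women effect. Amend section {20b} to allow this.

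One caution on combining these. With unequal residual variances and a single common treatment slope, the model weights women by inverse variance. Under the SDs assumed above the low strata would get 1/0.04 = 25 times the weight, and the common effect would shrink towards 0.9/26 ≈ 0.03. The all-women effect should therefore be the average of the stratum-specific effects weighted by stratum share, taken from the model with the three-way term.

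No new data are needed. The cost is a few more parameters, and the moderate-strata estimate rests on about 43 women and should be reported with its interval. The SHAPS analysis is unchanged.

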## Abstract

**Background:**

The perimenopausal transition is accompanied by psychiatric symptoms in over 10% of women. Symptoms commonly include depressed mood and anhedonia and less commonly include psychosis. Psychiatric symptoms have been linked to the depletion and/or variability of circulating estradiol, and estradiol treatment reduces perimenopausal anhedonia and psychosis in some women. Estrogen fluctuations may disrupt function in the mesolimbic reward system in some women, leading to psychiatric symptoms like anhedonia or psychosis. The Perimenopausal Effects of Estradiol on Anhedonia and Psychosis Study (PEEPs) is a mechanistic clinical trial that aims to (1) identify relationships between perimenopausal-onset anhedonia and psychosis and neuromolecular markers of mesolimbic reward responses and (2) determine the extent to which estradiol treatment-induced changes in mesolimbic reward responses are associated with alleviation of perimenopausal onset anhedonia or psychosis.

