### Objectives {7}

The primary endpoints of the PEEPs study are mechanistic, measured via neural and molecular reward responses. Using simultaneous PET-MR imaging, this study will examine striatal blood oxygen level-dependent (BOLD) activation to rewards, measured with fMRI, and reward-related striatal dopamine release, measured with [^11^C]raclopride PET. To elicit a reward response, participants will complete a monetary incentive delay (MID) task during imaging. This task has previously shown sensitivity to altered reward-related dopamine release in a transdiagnostic anhedonia sample [35]. The first study objective aims to characterize the relationship between striatal reward responses and perimenopausal-onset anhedonia and psychosis symptoms at baseline. We hypothesize that anhedonia symptoms will be linked to reduced striatal BOLD activation and decreased task-related dopamine release to rewards. In contrast, we expect psychosis symptoms will be linked to increased striatal activation to rewards and higher baseline (tonic) dopamine release. The second objective of this trial will be to determine the effects of estradiol versus a placebo on perimenopausal-onset anhedonia and psychosis symptoms as well as striatal reward responses. We expect the effects of estradiol will be greater than placebo, as indexed by alleviation of anhedonia and psychosis symptoms and normalization of striatal reward response. We further hypothesize that reductions in *anhedonia* symptoms in the estradiol treatment group will be linked to increased striatal activation and increased dopamine release to rewards, whereas reductions in *psychosis* symptoms will be associated with decreased striatal activation to rewards and reduced tonic dopamine release.

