### Trial design {8}

A parallel-group, randomized, placebo-controlled, double-blind superiority trial will be used to determine the effects of 3 weeks of estradiol treatment, relative to placebo, on perimenopausal-onset anhedonia and/or psychosis symptoms and neural and molecular reward responses. The study will enroll 100 participants with at least clinically significant anhedonia, including a range of mild-to-moderate anhedonia and absent-to-moderate psychosis symptoms. Based on screen failures and dropout rates in our prior studies involving PET-MR and perimenopausal depression, we expect to obtain analyzable data from at least 85 participants with two PET-MR scans each.

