### Sample size {14}

For the first study objective, correlation analyses will be used to examine associations between baseline clinical measures (anhedonia and psychosis) and neural markers (striatal BOLD activation and baseline/reward-related dopamine release). Power analysis suggests that a sample of 85 participants will yield approximately 80% power to detect small-to-medium effects (smallest detectible *r*=.27) at *α*=.05, which is consistent with our in-house pilot data. With respect to the study’s second objective, longitudinal mixed models will be used to examine the effects of estradiol versus placebo on (1) symptom trajectories measured across four timepoints and (2) neural/molecular markers across two timepoints. A sample of 85 participants will yield 80% power to detect small-to-medium effects, with the smallest detectible effect *f*^2^=.05 for clinical outcomes and *f*^2^=.07 for brain changes. To determine associations between changes in symptoms and changes in neural/molecular reward response in the estradiol treatment group, intercorrelations will be examined in primary analyses. A sample of 43 participants will yield 80% power to detect medium-to-large effects, with the smallest detectible effect size of *r*=.41.

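### The symptom–brain change association is planned in the estradiol arm only, so it cannot separate co-variation under estradiol from co-variation that also occurs on placebo

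*Protocol article*

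**What the plan says.** The Abstract (Background) gives the second aim as to "determine the extent to which estradiol treatment-induced changes in mesolimbic reward responses are associated with alleviation of perimenopausal onset anhedonia or psychosis". The statistical methods section {20a} limits the analysis of that link to one arm: "Within the estradiol treatment group only, we will examine how biomarkers of reward response predict changes in clinical outcome measures". The Sample size section {14} repeats the restriction and places the analysis among the primary ones: "To determine associations between changes in symptoms and changes in neural/molecular reward response in the estradiol treatment group, intercorrelations will be examined". It sizes the analysis as follows: "A sample of 43 participants will yield 80% power to detect medium-to-large effects", "with the smallest detectible effect size of *r*=.41". The Objectives section {7} also words the hypothesis inside one arm, expecting that reductions in anhedonia "symptoms in the estradiol treatment group will be linked to increased striatal activation and increased dopamine release to rewards".

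Imaging is not restricted by arm. Under Intervention description {11a}, "participants will complete PET-MR scans at baseline and the end of treatment to examine neural and molecular responses to rewards", and the same section schedules four weekly clinical assessments. Trial design {8} adds: "we expect to obtain analyzable data from at least 85 participants with two PET-MR scans each".

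The between-arm analyses in {20a} are mixed models of time, group and their interaction, fitted separately to each clinical and each brain outcome. A later sentence plans mixed models in which brain change predicts symptom trajectories. It names no arm term, and whether it covers both arms is not clear. The Abstract (Methods) ties these models to trajectories in response to estradiol.

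**The concern.** A woman's change from baseline while on estradiol is not the same as change caused by estradiol. It also contains placebo response, which the section on choice of comparators {6b} gives as the reason for having a placebo arm, and natural hormone fluctuation, which the Introduction treats as a driver of both symptoms and reward function. Either can make symptom change and striatal change move together without the patch.

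The placebo arm measures that background co-variation, and no stated analysis uses it for this purpose. A significant correlation in the estradiol arm could then be read as showing how estradiol works, when the same correlation might be present on placebo. The Discussion part of the Abstract speaks of mechanisms by which estradiol improves symptoms, so that reading is a natural one.

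**Working it through.** **Inputs.** Estradiol arm n=43, r=.41 and 80% power, from Sample size {14}. Total analysable N=85, from Trial design {8}. Assumptions: 85−43=42 placebo participants, because the allocation ratio is not stated; α=.05, which is stated for the first objective only; two-sided testing, because sidedness is not stated. No covariates and no correction for multiple comparisons are applied.

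**Step 1: the plan's own figure.** With Fisher's z, power = Φ(atanh(r)·√(n−3) − 1.960).
- atanh(.41)=0.4356 and √40=6.325, so power = Φ(2.755−1.960) = Φ(0.795) = 78.7%.
- Noncentral t gives 82.1%, and 20,000 simulated trials give 79.8%.
- One-sided testing would give 86.7%.

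The stated 80% is therefore reproduced as a two-sided figure.

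**Step 2: can the planned test tell the two situations apart?** Each scenario was simulated 20,000 times with 43 and 42 participants and unit variances. The interaction is the arm by brain-change term.

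| True r, estradiol / placebo | Planned within-arm test significant | Interaction significant |
|---|---|---|
| .41 / .41 | 79.8% | 4.9% |
| .41 / 0 | 79.9% | 48.0% |

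The planned test behaves identically in both rows, as it must, because it never sees the placebo data. The table shows whether the association differs by arm. It does not show whether estradiol acts through the brain measure (Step 4).

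**Step 3: precision of the between-arm comparison.** The standard error of a difference of two Fisher z values is √(1/40+1/39) = 0.225.
- .41 versus 0: Φ(0.4356/0.225 − 1.960) = 49%.
- .41 versus .10: 32%.
- .41 versus .20: 18%.
- Smallest difference with 80% power: (1.960+0.842)×0.225 = 0.630 on the z scale, which is tanh(0.630) = .56 versus 0.
- For 80% power at .41 versus 0: 2×(2.802/0.4356)²+3, about 86 analysable participants per arm.
- Half-width of a 95% interval for the difference: 1.960×0.225 = 0.44 on the z scale.

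**Step 4: what a common slope means.** Suppose estradiol shifts the mean striatal response by δ, and each unit of striatal change moves symptoms by β in either arm. The brain–symptom slope is then β in both arms and the interaction is zero, yet δ×β of the symptom effect passes through the brain measure. Shared background co-variation can also give equal slopes. The interaction alone cannot separate these cases; the randomised effect of arm on the brain measure (δ) has to be read beside the slopes.

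**The case against.** The strongest defence is that the plan is consistent within itself. The hypothesis in Objectives {7} is worded within the estradiol group, the sample size is set for that group, and {20a} tests it there. The mismatch is with the aim in the Abstract, and even that aim speaks only of association. This stands. It shows that the analysis fits the hypothesis, but not that the hypothesis fits the aim.

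A reader might infer that the trial gives up its randomised control for its mechanistic question. The documents do not support that. The primary mechanistic endpoint is the reward response itself, and the time by group models test it, and both symptom outcomes, across arms. Only the link between the two lacks a comparison.

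A reader might also infer that equal correlations in both arms would refute a mechanism. Step 4 shows that they would not.

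Other non-drug explanations are weaker than they look. Selection on SHAPS causes regression to the mean in symptom scores, but residualised gain removes the linear dependence on baseline symptoms and nobody is selected on a brain measure. Task practice affects the scans, with no stated route to symptoms.

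Finally, a reader might see a mismatch between residualised gain for symptoms and change scores for the brain. The first belongs to the correlations and the second to the trajectory models. How brain change is formed for the correlations is not stated, so no inconsistency is shown.

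**Conclusion.** The point holds in a limited form. The planned association cannot distinguish co-variation under estradiol from co-variation that placebo participants also show, although the aim concerns estradiol-induced change and the placebo data are scheduled. The planned test has about 80% power at r=.41 whatever the placebo correlation is.

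Adding the placebo arm makes the comparison visible but not precise: about 49% power at .41 versus 0, and 80% only at about .56 versus 0. These figures assume 43 and 42 analysable participants, two-sided α=.05, equal variances in the arms and no multiplicity correction; any correction would lower them. Brain change is measured after randomisation, so the association remains observational even with both arms in the model.

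**What to change.** Fit the association in both arms: end-of-treatment symptom score (or trajectory) on baseline symptom, baseline brain measure, brain change, arm, and arm by brain change. Report the slope in each arm and their difference with confidence intervals, as estimation and not as a pass-or-fail test. State in advance that a null interaction is not evidence against a mechanism, and that the slopes will be interpreted together with the randomised effect of arm on the brain measure. Where the results do not support more, word the conclusion as a within-arm association.

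Two wording points follow. State that the trajectory models include both arms. Also define the mechanistic per-protocol set in {20a} by completion of the allocated treatment, because as written it requires three weeks of estradiol and would, read literally, exclude placebo participants.

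The cost is a change of analysis text and some extra modelling. No visit or scan is added, and with recruitment running to the end of 2026 the measurements are already scheduled. The downside is that the between-arm contrast will be imprecise and the mechanistic claim may have to be more modest.
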